## Abstract

**Background:**

The use of vestibular rehabilitation principles in the management of gaze and postural stability impairments in people with multiple sclerosis (PwMS) has shown promise in pilot work completed in our lab and in a recently published randomized clinical trial (RCT). However, further work is needed to fully quantify the gaze and postural impairments present in people with multiple sclerosis and how they respond to rehabilitation.

**Methods/design:**

The study is a single blind RCT designed to examine the benefit of a gaze and postural stability (GPS) intervention program compared to a standard of care (SOC) rehabilitation program in dizzy and balance impaired PwMS. Outcomes will be collected across the domains of body structure and function, activity, and participation as classified by the World Health Organization International Classification of Functioning, Disability, and Health (ICF). Our primary outcomes are the Dizziness Handicap Inventory (DHI) and the Functional Gait Assessment (FGA). Secondary outcomes include other measures of gaze and postural stability, fatigue, and functional mobility. Participants who are interested and eligible for enrollment will be consented prior to completing a baseline assessment. Following the baseline assessment each participant will be randomized to either the GPS or SOC intervention group and will complete a 6 week treatment period. During the treatment period, both groups will participate in guided exercise 3x/week. Following the treatment period participants will be asked to return for a post-treatment evaluation and again for a follow-up assessment 1 month later. We anticipate enrolling 50 participants.

**Discussion:**

This study will be an innovative RCT that will utilize gaze and postural stability metrics to assess the efficacy of vestibular rehabilitation in PwMS. It will build on previous work by examining measures across the ICF and improve the current evidence base for treating PwMS.

**Trial registration:**

ClinicalTrials.gov, May 29th 2018, NCT03521557.

## Background

Multiple Sclerosis is a progressive neurologic disease with a poorly defined etiology that has been linked to genetic, nutritional, infectious, and environmental factors [1]. The study of the disease is further confounded by the varying levels of progression that are categorized into four typical designations based on histologic and clinical presentation: Relapsing Remitting (RRMS), Secondary Relapsing (SRMS), Secondary Progressive (SPMS), and Primary Progressive (PPMS) [1]. Across this spectrum of disease severity the prevalence of MS has been reported to range from 83 to 146/100,000 in North America and Europe, making it the most commonly occurring chronic inflammatory disorder of the central nervous system [1].

Rehabilitative treatment for people living with Multiple Sclerosis (MS) typically includes cardiovascular, strength, and balance training. A large number of clinical trials have demonstrated the benefits of these exercise interventions [2–4]. However, due to the variable presentation in MS and the wide range of symptoms, no single intervention approach has been identified as the gold standard. Therefore, treatment is typically individualized depending upon the individual patient’s signs and symptoms. Among the many presentations common in people with MS are complaints of dizziness, unsteadiness, and poor balance. While these symptoms may have contributions from altered muscle performance, dysfunctions of the vestibular system are a real possibility and often overlooked [5]. In fact, these symptoms have been reported to occur in between 30 and 59% of people living with MS. [6, 7] Unfortunately, until relatively recently, studies have not been designed to examine the benefits of vestibular focused exercises to improve outcomes in people with MS. Furthermore, because of the sparsity of studies, the optimum dosing, exercise type, and duration of vestibular rehabilitation in MS remains unknown.

Recently published studies have taken critical first steps in exploring the use of vestibular based rehabilitation in patients with MS who have complaints of dizziness and poor balance [8, 9]. These studies demonstrated significant improvements in outcomes including patient reported dizziness and scores of the sensory organization test following participation in a vestibular based rehabilitation protocol. To expand on this work, we have designed the current study to examine the use of a vestibular rehabilitation protocol to improve self-reports of dizziness handicap, dynamic stability during gait, as well as gaze and postural stability outcomes. The measures used in this study were chosen to reflect domains of disablement from across the spectrum of the World Health Organization International Classification of Functioning, Disability, and Health (ICF) [10]. Specifically, the outcomes in the domain of body structure and function are measures of the vestibulo-ocular reflex (gaze stability) and the vestibulo-spinal reflex (postural stability). The Activity domain is measured by examining each participant’s ability to stabilize vision during movement and maintain postural stability during various tasks. Participation will be examined using questionnaires pertaining to limitations during life situations as a result of poor gaze and/or postural stability.

The purpose of this manuscript is to summarize the protocol (study design, participants, outcome measures, intervention details, and planned statistical analysis) to be used in a prospective randomized clinical trial (RCT). The objectives of this RCT will be to (1) characterize baseline gaze and postural stability limitations across the domains of the ICF in individuals with MS, and (2) to systematically test the efficacy of a vestibular rehabilitation approach at improving gaze and postural stability in individuals with MS compared to a standard of care intervention.

## Methods/design

Study design: The proposed project is designed as a single blind RCT. Participants in the trial will be tested at baseline, 6-weeks (post-intervention), and 10-weeks (follow-up). The intervention period lasts for a total of 6 weeks over which participants in both control and intervention groups participate in 18 visits of guided treatment at a frequency of 3x/week. (Fig. 1).

**Fig. 1 Fig1:**
[figure not shown]
Study flowchart demonstrating the study procedures from screening through study completion

Participants/enrollment: Recruitment will occur through collaborative university and community neurologist clinics, university physical therapy clinics, and through community advertising including advertising through the National Multiple Sclerosis Society. Included participants will be between the ages of 20 and 75, have neurologist diagnosed MS, able to tolerate up to 5 min of continuous head movement, and have dizziness or impaired balance determined by having either experienced ≥2 falls in the last year, a Dizziness Handicap Inventory score > 0, an Activities Balance Confidence scale score < 80%, or a Dynamic Gait Index score < 19. Participants will be excluded if they have neurologic diagnosis other than MS, the presence of peripheral vestibular pathology (i.e., BPPV, hypofunction, or Meniere’s disease), have experienced an exacerbation in MS symptoms within the last 8 weeks, or have an orthopedic, cardiovascular, or other comorbidity that limits exercise participation.

### Power/sample size calculation

Using data from: 1) our pilot research on gaze and postural stability in persons with MS [8] and 2) spatial and temporal measures from previous vestibular research examining the response to task specific training [11–14], we estimated an effect size of d = 0.25 for the DHI with the correlation between baseline and follow-up measurements as 0.50. Twenty participants in each arm provides us with greater than 80% power and 2-sided α = 0.05 to detect a difference between groups on the DHI. We will enroll 50 individuals with MS from various sources to ensure adequate power to examine both DHI and FGA.

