### Statistical analysis plan

All data will be initially analyzed to determine if assumptions for parametric analysis are met. Decisions regarding appropriate statistical tests will be made based on the normalcy of the data. Corrections for increased type 1 error risk will be performed separately for the data within each specific aim. Post-hoc power and effect size will be calculated for all tests to inform the sample sizes of future studies.

Analyses of longitudinal outcomes will be performed using mixed effects models in which results are robust to missing data as long as the pattern of missingness conforms to the missing at random (MAR) assumption [54]. If more than 10% of follow-up measurements are missing for primary or any of the main secondary outcomes at any of the follow-up visits, sensitivity analyses will be performed after applying multiple imputation to impute missing data under models incorporating predictors of missingness and/or the outcome variables [55].

For the primary outcomes (DHI and FGA) we will apply a linear mixed model [55] to compare mean scores at the post-test and follow-up assessments between the GPS and SOC groups after controlling for baseline scores. Statistical inferences will be performed using restricted maximum likelihood estimation under an unstructured covariance model to account for serial correlations among repeated measurements. The fixed effects terms will include the baseline scores, follow-up visit (as a categorical variable), treatment assignment, and the interaction between follow-up visit and treatment assignment. For secondary outcomes, similar mixed effects analyses will be applied to evaluate the effects of the GPS intervention compared to SOC on the ABC, Mini-BESTest, DVA, vHIT, and reactive postural response tests, adjusting in each case for initial levels of the dependent variable. Monitoring for safety will be conducted throughout the study, investigating all possible unanticipated safety events.

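### The stated power above 80% for d = 0.25 on the DHI is wrong: 20 per arm gives about 14% and 25 per arm about 17% for the planned baseline-adjusted comparison at one visit

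*Protocol article*

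**What the plan says.** The section Power/sample size calculation gives every input. The effect: "we estimated an effect size of d = 0.25 for the DHI". The correlation: "with the correlation between baseline and follow-up measurements as 0.50". The size and claimed power: "Twenty participants in each arm provides us with greater than 80% power". The test level and target: "2-sided α = 0.05 to detect a difference between groups on the DHI". It then states: "We will enroll 50 individuals with MS from various sources to ensure adequate power to examine both DHI and FGA".

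The section Statistical analysis plan sets the analysis for both primary outcomes. A linear mixed model will "compare mean scores at the post-test and follow-up assessments between the GPS and SOC groups after controlling for baseline scores", at 6 and 10 weeks. On the model terms it says: "The fixed effects terms will include the baseline scores, follow-up visit (as a categorical variable), treatment assignment, and the interaction" of visit with treatment. The same section says that type 1 error will be corrected within each aim, without naming the method.

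**The concern.** By convention d = 0.25 is a small effect, a quarter of a standard deviation. Twenty per arm is a small trial, and a correlation of 0.50 with baseline removes only a quarter of the outcome variance. Those three facts do not fit with power above 80%.

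The DHI is a primary outcome, and this is the only effect size the document gives to justify its sample size. If the figure is wrong, the trial is described as able to detect a quarter-SD benefit when it can reliably detect only one about three times as large. The expected precision shows the same: at one visit the 95% confidence interval would extend about 0.55 SD either side of the estimate with 20 per arm, or 0.49 SD with 25. An inconclusive result could therefore not rule out a benefit of 0.25 SD.

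**Working it through.** **Inputs from the document:** d = 0.25; r = 0.50 (baseline to follow-up); two-sided alpha 0.05; n = 20 per arm, or 25 per arm from 50 enrolled. Equal allocation of the 50 is an assumption. All effects are in units of the raw DHI standard deviation.

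**1. Attempt to reproduce the claim with d = 0.25.** The standard error of the group difference is k × sqrt(2/n), where k is the SD multiplier of the analysis. Power comes from the noncentral t distribution with noncentrality d / (k × sqrt(2/n)).

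- Unadjusted follow-up score: k = 1. Change score: k = sqrt(2(1 − r)) = 1.
- Baseline-adjusted, one visit: k = sqrt(1 − r²) = sqrt(0.75) = 0.866, with 2n − 3 degrees of freedom.

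For the planned adjusted comparison at one visit:

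- n = 20: standard error 0.866 × sqrt(2/20) = 0.274; noncentrality 0.25/0.274 = 0.913; critical t (37 df) 2.026; power **14.4%**.
- n = 25: standard error 0.866 × sqrt(2/25) = 0.245; noncentrality 0.25/0.245 = 1.021; critical t (47 df) 2.012; power **17.0%**.

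**2. Using both follow-up visits.** If the 6- and 10-week scores are averaged, k = sqrt((1 + q)/2 − r²), where q is the correlation between the two visits. The document does not give q, so a range is shown.

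| Analysis, d = 0.25, two-sided 0.05 | 20 per arm | 25 per arm |
|---|---|---|
| Unadjusted or change score | 12.0% | 13.9% |
| Baseline-adjusted, one visit | 14.4% | 17.0% |
| Baseline-adjusted, mean of two visits, q = 0.9 (k = 0.837) | 15% | 18% |
| Baseline-adjusted, mean of two visits, q = 0.5 (k = 0.707) | 19% | 23% |

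Other variants that keep d = 0.25 also fall short. One-sided tests with 20 per arm give 19% to 29%. A paired within-group test gives 18.6% with 20 people and 41.0% with 50.

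**3. What 80% would require.** At d = 0.25 and r = 0.50, about 190 per arm at one visit, or about 127 per arm on the mean of two visits with q = 0.5. With 20 per arm at one visit, r would have to be about 0.96.

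**4. What the planned size can detect with 80% power (r = 0.50).**

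| | 20 completers per arm | 25 completers per arm |
|---|---|---|
| One visit, alpha 0.05 | 0.79 SD | 0.70 SD |
| One visit, alpha 0.025 | 0.87 SD | 0.78 SD |
| Mean of two visits, alpha 0.05, q = 0.5 to 0.9 | 0.64 to 0.76 SD | 0.57 to 0.68 SD |

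**5. Readings that do reproduce the claim.** Suppose 0.25 is Cohen's f for a group-by-time interaction in a repeated-measures ANOVA with N = 40, m time points and correlation 0.5. The noncentrality is f² × N × m / (1 − 0.5).

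- m = 2: 0.0625 × 40 × 2 / 0.5 = 10, on 1 and 38 df; power 86.9%.
- m = 3: 0.0625 × 40 × 3 / 0.5 = 15, on 2 and 76 df; power 93.5%.

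With two time points, f = 0.25 places each of the four cell means 0.25 SD from its no-interaction value, so the groups differ in change by 4 × 0.25 = 1.0 SD. As a check, a change-score t-test at 1.0 SD has noncentrality 1.0/sqrt(2/20) = 3.16, whose square is 10, as above.

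A second reading also exceeds 80%. If 0.25 is eta-squared, then f = sqrt(0.25/0.75) = 0.577 and d = 2 × 0.577 = 1.15, and a plain t-test with 20 per arm has about 94% power.

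**The case against.** The best defence is that the calculation was sound and only the label is wrong: 0.25 was some other effect-size metric. This is plausible, since the Cohen's f reading returns a figure above 80% with N = 40. It does not rescue the text. The document says d, and under the f reading with two time points the effect is a 1.0 SD difference in change, four times what is printed. That calculation is also for a different test from the planned model. If f = 0.25 is instead converted to d = 0.5, the adjusted comparison at one visit has only 42.8% power (20 per arm) or 51.6% (25 per arm).

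A reader might go further and infer that 0.25 must be a mislabelled Cohen's f. The documents do not support this. The eta-squared reading exceeds 80% too, the repeated-measures test of the time effect alone gives the same 87% and 94%, and the pilot data behind the figure are not shown.

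A reader might also infer that the trial makes no allowance for dropout, or that the Functional Gait Assessment (FGA) is underpowered. Neither follows. A condensed article may leave an attrition rate and an FGA effect size to the full protocol. Fifty exceeds the calculated 40 by ten, although the text gives the reason as power rather than dropout. Without an FGA effect size, the FGA half of the adequacy claim cannot be tested either way.

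Two cautions on the check itself do stand. The two-visit figures depend on an inter-visit correlation that the document does not give, and the analysis section fits a visit-by-treatment interaction without saying that visits will be averaged. A restated figure at alpha 0.05 would also be optimistic if the planned type 1 error correction applies to the two primary outcomes.

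**Conclusion.** The power statement is wrong as written, and the conclusion is firm. No analysis tried that keeps d = 0.25 comes near 80%. The one-visit results rest only on the document's own inputs, its baseline-adjusted analysis, complete data and, for 50 enrolled, equal allocation. The claim that 50 ensures adequate power therefore fails for the DHI at this effect. Splitting alpha to 0.025, as an illustration, would lower one-visit power to 8.8% (20 per arm) or 10.7% (25 per arm).

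Either the effect size or the power is misstated, and the document does not show which. The error concerns the description of what the trial can detect. It does not bias the treatment estimate or affect the type I error of the planned model, and nothing in the document says how a null result would be interpreted.

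**What to change.** Keep the sample size and replace the power sentence with one that follows from the inputs. For example: with 20 completers per arm the trial has 80% power for a standardised DHI difference of about 0.79 at one follow-up visit (baseline-adjusted, r = 0.50, two-sided 0.05), or about 0.70 with 25 per arm. Add that these become about 0.87 and 0.78 if alpha is split to 0.025 across the two primary outcomes.

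If 0.25 is not Cohen's d, name the metric and the test it belongs to, and give the equivalent DHI difference in SD units and in points.

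Withdraw the statement that 50 participants ensure adequate power for the DHI at d = 0.25.

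The cost is wording only. No participants are added and the design does not change, but the stated detectable effect becomes less favourable. The article's data availability statement says that data are still being collected and remain blinded, so the correction can be made before results are known.

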### Participants

Participants will be screened in-person or via telephone call for qualification in the study. If study inclusion is met, demographic information and disease history will be collected via interview at the baseline assessment. Following baseline testing participants will be randomized to receive either the standard of care (SOC) or gaze and postural stability (GPS) intervention. Randomization will be performed and delivered to the treatment team by an unblinded research coordinator, while all outcome assessors will remain blind to group assignment. All standardized outcome measures will be collected at each testing timepoint (baseline, post-intervention, follow-up). Intervention protocols for standard of care and gaze and postural stability interventions, as well as all outcome measures are described below.

### Confirmation of central vestibular pathology

The absence of PNS mediated vestibular dysfunction and the presence of CNS mediated vestibular dysfunction will be confirmed by a systematic process. First, we will conduct a focused history including signs and symptoms as well as treatment for *a prior* peripheral vestibular pathology [15]. Second, we will perform clinical testing to rule out peripheral causes of vestibular symptoms (Dix Hallpike and Roll Tests for vertical and horizontal canal BPPV respectively; clinical head impulse testing to test for unilateral or bilateral hypofunction; observation of the presence or absence of direction fixed spontaneous nystagmus with fixation removed). Third, we will confirm the presence of CNS mediated oculomotor deficits (saccadic smooth pursuit, dysmetric saccades, abnormal vestibular ocular reflex [VOR] cancellation) and a perverted head shake nystagmus (fixation removed) [16]. Lastly, we will document the presence or absence of VOR gain deficits and saccadic corrections via head impulse testing that did not follow a pattern consistent with peripheral vestibular pathology [17].

### Gaze and postural stability (experimental) intervention

The GPS intervention is specifically designed to focus on gradually increasing difficulty of gaze and postural stability exercises. The protocol frequency, duration and components were based off of previous intervention trials conducted on peripheral pathology [9, 11–13, 18], as well as, pilot work performed on PwMS [8]. For specific detail regarding the treatment protocol and progression refer to Table 1.

**Table 1 Tab1:** Specific treatment and progression for experimental group receiving gaze and postural stability (GPS) intervention

Week	Gaze and Postural Stability (GPS) Group Intervention
1	Gaze stability: aVOR × 1 far target, Performed at 2 Hz (metronome paced) × 2 min × 5 reps. Postural stability: standing with static BOS, static COM, static head positions out of neutral (looking, up, down, right, left)
2	Gaze stability: aVOR × 1 near and far targets, 2 targets. Performed at 2 Hz (metronome paced) × 2 min × 5 reps. Postural stability: standing with static BOS, dynamic COM, head rotations (looking, up, down, right, left)
3	Gaze stability: aVOR × 1 near and far targets, aVOR × 2, 2 targets, Performed at 2 Hz (metronome paced) × 2 min × 5 reps. Postural stability: standing / walking compliant surface, static head positions out of neutral (looking, up, down, right, left)
4	Gaze stability: aVOR × 1 near and far targets, aVOR × 2, 2 targets. Performed at 2 Hz (metronome paced) × 2 min × 5 reps. Postural stability: standing / walking compliant surface, head rotations (looking, up, down, right, left)
5	Gaze stability: aVOR × 1 while walking, aVOR × 2 while standing. Performed at 2 Hz (metronome paced) × 2 min × 5 reps. Postural stability: standing / walking, eyes open / closed, head rotations (looking, up, down, right, left)
6	Gaze stability: aVOR × 1 while walking, aVOR × 2 while standing, 2 targets, imaginary target. Performed at 2 Hz (metronome paced) × 2 min × 5 reps. Postural stability: standing / walking, eyes open / closed, head rotations (looking, up, down, right, left)

Progression of exercises will only occur if participants are able to successfully complete the current weeks exercises. aVOR ×1 = horizontal / vertical head motions while maintaining focus on a stationary visual target; Far target = target at 3 m; Near target = target at 1 m; 2 targets = Participant first moves eyes to a target and while maintaining focus on target, moves head to face target; Head rotations = Participant rotates head side to side or up and down; Static base of support (BOS) = feet in place; Static Center of Mass (COM) = stationary body; Dynamic COM = moving body; Dynamic BOS = moving BOS, such as in walking

### Standard of care intervention

The SOC intervention is designed to focus on improving endurance and lower extremity muscular strength. The protocol was based off of documented evidence from previous intervention trials with PwMS [3, 4], as well as, recent evidence from experimental and meta-analytic studies documenting the benefits of exercise (aerobic and resistance) to improve walking ability in people with MS [19–21]. For specific detail regarding the treatment protocol and progression please refer to Table 2.

**Table 2 Tab2:** Specific treatment and progression for standard care exercise group receiving aerobic and resistance intervention

Week	Standard Care Exercise Group Intervention
1–6	Aerobic Exercise at a moderate exercise intensity (13 on a 20 point Borg Scale) × 30 min^a^; 3x/week Resistance exercise: Lower extremity leg press / concentric at 50% 1RM^b^ × 3 sets × 20 repetitions; 3x/week Lower extremity heel raises / concentric at 50% 1RM** × 3 sets × 20 repetitions; 3x/week

^a^Aerobic Exercise will be performed on a seated NuStep Upper Extremity/Lower Extremity Ergometer. This mode of exercise is chosen because it has been shown to elicit sufficient aerobic challenge while at the same time minimizing postural/vestibular demands because of the sitting position and back support

^b^Lower extremity resistance training will be performed on a seated leg press (Tuffstuff, Pomona, CA). This mode of exercise is chosen because it has been shown to strengthen lower extremity extensors relevant for gait while at the same time minimizing postural / vestibular demands because of the sitting position and back support

